## Abstract

**Background:**

Dental caries is one of the most prevalent non-communicable disease globally and can have serious health sequelae impacting negatively on quality of life. In the UK most adults experience dental caries during their lifetime and the 2009 Adult Dental Health Survey reported that 85% of adults have at least one dental restoration. Conservative removal of tooth tissue for both primary and secondary caries reduces the risk of failure due to tooth-restoration, complex fracture as well as remaining tooth surfaces being less vulnerable to further caries. However, despite its prevalence there is no consensus on how much caries to remove prior to placing a restoration to achieve optimal outcomes. Evidence for selective compared to complete or near-complete caries removal suggests there may be benefits for selective removal in sustaining tooth vitality, therefore avoiding abscess formation and pain, so eliminating the need for more complex and costly treatment or eventual tooth loss. However, the evidence is of low scientific quality and mainly gleaned from studies in primary teeth.

**Method:**

This is a pragmatic, multi-centre, two-arm patient randomised controlled clinical trial including an internal pilot set in primary dental care in Scotland and England. Dental health professionals will recruit 623 participants over 12-years of age with deep carious lesions in their permanent posterior teeth. Participants will have a single tooth randomised to either the selective caries removal or complete caries removal treatment arm. Baseline measures and outcome data (during the 3-year follow-up period) will be assessed through clinical examination, patient questionnaires and NHS databases. A mixed-method process evaluation will complement the clinical and economic outcome evaluation and examine implementation, mechanisms of impact and context. The primary outcome at three years is sustained tooth vitality. The primary economic outcome is net benefit modelled over a lifetime horizon. Clinical secondary outcomes include pulp exposure, progession of caries, restoration failure; as well as patient-centred and economic outcomes.

**Discussion:**

SCRiPT will provide evidence for the most clinically effective and cost-beneficial approach to managing deep carious lesions in permanent posterior teeth in primary care. This will support general dental practitioners, patients and policy makers in decision making.

*Trial Registration *Trial registry: ISRCTN. Trial registration number: ISRCTN76503940. Date of Registration: 30.10.2019. URL of trial registry record: https://www.isrctn.com/ISRCTN76503940?q=ISRCTN76503940%20&filters=&sort=&offset=1&totalResults=1&page=1&pageSize=10&searchType=basic-search.

**Supplementary Information:**

The online version contains supplementary material available at 10.1186/s12903-021-01637-6.

## Background

Dental caries in permanent teeth is a widespread and costly public health problem. Globally, it is one of the most prevalent non-communicable disease and can have serious health sequelae which can impact negatively on quality of life and productivity[1–5]. In the UK most adults experience dental caries during their lifetime and the 2009 Adult Dental Health Survey reported that 85% of adults have at least one restoration [6]. The removal of less tooth tissue for both primary and secondary caries reduces the risk of failure due to tooth-restoration fracture, complex fracture and the surfaces are less vulnerable to further caries [7]. Furthermore, smaller cavities simplify the operative procedure when placing restorations, so improving their long-term viability.

However, despite the prevalence of this non- communicable disease there is no consensus about how much caries affected tooth tissue to remove prior to placing a filling to achieve optimal patient outcomes. Evidence for selective compared to complete or near-complete caries removal suggests there may be benefits for selective removal in sustaining tooth vitality therefore avoiding abscess formation and pain, and eliminating the need for more complex, costly treatment or eventual tooth loss. However, the evidence is of low scientific quality and mainly gleaned from studies on primary teeth.

The majority of current NHS treatment is managing failed restorations and their consequences moving to increasingly invasive and costly treatments. NHS expenditure on primary and secondary dental care in England approximates to £3.4bn per year, with over one million patient contacts weekly. Many of these contacts relate to treatment of caries. In 2016/17 in England, there were over 7m permanent fillings, over 2m extractions and around 1.5 m endodontic treatments, crowns, inlays or bridges provided to adult NHS patients in primary dental care. The total value of these treatments was about £1.27 bn, with a significant burden on both patients (~£635 m) and the NHS (~£639–£290 m for fee-paying and a further £349 m for exempt patients) [8] . A similar pattern of spend has been observed in Scotland for 2017 [9]. This does not take into account the dental treatment provided in private practice or the costs of NHS treatments delivered in secondary care.

The importance of this topic has been highlighted both by patients and general dental practitioners. General dental practitioners within the Scottish Dental Practice Based Research Network (http://www.sdpbrn.org.uk/) in 2011 voted this as the top research priority. More recently, focus groups and interviews with general dental practitioners followed by a national online survey of dental practitioners, which was conducted as part of this proposal, have established the current importance of the topic and informed the trial design of SCRIPT. The 320 survey participants demonstrated considerable variation in practice with 3% reporting they always perform selective caries removal and 13% reporting they never perform selective carious tissue removal. The primary outcome in the SCRIPT trial was considered to be important by 99% of participants and their free text comments clearly demonstrate the current professional uncertainty around how best to manage patients with deep carious lesions—“*would be willing to use selective caries removal if there was proof it does no harm” and “I'd be very keen to see more research in this area and would put it to use in my day to day practice.”*

In this trial, in addition to adults, young people between the ages of 12 years and 15 years will be included because the 2013 UK child dental health survey reported that nearly a half (46%) of 15 year olds and a third (34%) of 12-year-olds had "obvious decay experience" in their permanent teeth^12^. Of these a fifth (19%) of 12-year-olds and 15-year-olds (21%) had decay into dentine requiring treatment. Toothache was experienced by 18% of 12-year-olds and 15% of 15-year-olds. This suggests that the burden of dental caries is very high in this group and therefore including this age group in the trial would generate evidence of acceptability and potential issues related to actual treatment provision. Such evidence would help the dental practitioners in primary care to adopt minimally invasive approaches to carious tissue removal especially when the recent EU directive has recommended not to use amalgam fillings in under 15-year-olds [10].

This was further highlighted by a research priority setting exercise conducted with patients at a general dental practice in Derbyshire with the greatest potential benefit seen for the young people. A Patient and Public Involvement (PPI) group at the Health Services Research Unit (HSRU) in Aberdeen felt that development of such conservative techniques was very important as they could improve both the health and dental experience of patients. Overall, new evidence investigating whether a procedure involving sealing in decay in reduces the chances of teeth being lost and reduces the chance of painful episodes and further complex treatment like root canal treatment would be important and welcomed by patients.

Randomised controlled clinical trials and systematic reviews have concluded that selective caries removal (SCR) may offer benefits, but the evidence on managing deep caries in permanent teeth is weak and biased [11–14]. Schwendicke et al. [11] found a significant risk reduction for pulp exposure (OR 0.31 [0.19–0.49]), but pulp symptoms (OR 0.58 [0.31–1.10]) and risk of restoration failure (OR 0.97 [0.64–1.46]) were inconclusive (n=1,257). Similarly, for selective caries removal, Ricketts et al. [14] found a significant risk reduction for pulp exposure (OR 0.23 [0.08–0.69]), but again pulp symptoms (OR 0.27 [0.05–1.60]) and risk of failure were inconclusive (n=345 in the partial caries analysis of primary and permanent teeth). Quality of the evidence is judged to be poor scientifically and most of the included studies were conducted solely on children with short term follow-up [15–17], used less durable materials [16, 18] or included more aggressive complete caries removal (CCR) interventions to “hard” dentine [13, 19] than would be present in UK NHS.

Bjørndal et al. [12] followed-up for 5 years a 2-staged (stepwise) carious tissue removal protocol on lesions spreading into the pulpal quarter of dentine (n=239). Pulp exposure rate was lower in this stepwise removal protocol (21.2% vs. 35.5%; p = 0.014) and more successful (60.2% vs 46.3%) (p = 0.031) when pulp exposures were classed as failure. The trial has limited generalizability to SCRIPT’s context and patients: it recruited participants with more severe caries and its two interventions differed from SCRIPT’s. Their partial approach (2-step) was similar to CCR; their CCR approach was more aggressive than the one we propose to use, excavating “hard” dentine. Therefore, more evidence is needed about the performance of a minimally invasive option of SCR in the NHS and about whether dentists will adopt it. There is one ongoing trial in France [20] looking at this research question in a secondary care setting. Personal communication with the trial team confirmed they had experienced a merger (contamination) of the two technologies (i.e. the two techniques undertaken by an individual dentist tended to become more similar dependent upon their initial skills and preferences). The trial has had more than 30% loss to follow-up. The authors believe that is due to the secondary care setting where patients are usually transient and short term. Our research robustly monitors and minimises the risk of the technologies merging, and most patient participants are routine attenders at their dental practice.

Therefore, this research is important to establish whether SCR will sustain tooth vitality and reduce the need for complex, costly treatment including root canal treatment, crowns, extractions, bridgework or implants [21]. In addition to potential cost savings, this reduced treatment need would be expected to improve quality of life and reduce anxiety and stress.

The risk to participants is low as both treatments are utilised in NHS practice albeit that SCR is relatively under-employed. For SCR, which is a minimally invasive treatment, the perceived risk is the residual caries alone may lead to further deterioration of the tooth. The risks from CCR are already managed within existing dental practice so the trial does not impose any new risks. Risk in both arms will be monitored as part of the trial as the primary and some secondary outcomes directly measure the impact of each treatment.

## Methods/design

This is a pragmatic, primary dental care, multi-centre, single-masked, two-arm patient randomised controlld trial including an internal pilot, comparing the clinical-effectiveness and cost–benefit of Selective Caries Removal (SCR) with Complete Caries Removal (CCR) in permanent posterior teeth in participants aged 12 years and over.

Follow-up will last at least 3 years and will be conducted in multiple sites across the UK. The design includes an internal pilot to assess the recruitment of practices and participants and monitor compliance with the clinical protocol and acceptability for patients and clinicians (Fig. 1).

**Fig. 1 Fig1:**
[figure not shown]
A flow diagram illustrating the SCRiPT Trial design. *The study is statistically powered so that up to 25% of participants in total could receive the non-allocated procedure. Processes are in place to minimise this from occurring

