## Analysis plan

### Sample size calculation

The sample size calculation is event-based. We aim to detect an absolute improvement in sustained tooth vitality at three years of 12% from 80% (CCR) to 92% (SCR). The control rate of 80% is based upon the existing evidence base, clinical experience and confirmed by Scottish tooth-level routine data. As described in Sect. 2.1 above, the current evidence base gives rates of pulpal exposure that are higher than those seen in UK NHS and therefore our rate of sustained tooth vitality will be higher than observed in those studies. Bjørndal 2017 [12] presented a tooth vitality rate of approximately 80% at 3 years for two-step selective restoration in lesions that were deeper than those in this trial. The two-step procedure is more similar to a CCR than the SCR in our trial. The Scottish tooth specific data demonstrated that of 459,648 teeth that required a three surface restoration in 2013, 6.6% had received further endodontic treatment or were extracted at 3 years follow-up. These teeth however, could be at any level of dentine involvement and it is not possible to identify the level of involvement in the routine data. Therefore, as the study is interested in only teeth with involvement in the pulpal third of dentine, it has been estimated that the number of events may be three times larger. There is little empirical evidence to inform the expected size of an important effect. A target difference of 12% was judged clinically important and plausible by both dentists and PPI partners. The target difference of 12% was also informed by the difference observed in Bjørndal 2017 [12] which was 13.7% at 5 years. However, as this is a patient RCT there are concerns around contamination (participants receive the intervention that they were not randomly allocated to). The team conservatively have allowed for up to 25% contamination and therefore the sample size for SCRiPT aims to detect an absolute improvement of 9%; from 83 to 92% at three years. Recruitment of 623 participants (71 events) will detect a hazard ratio of 0.42 between experimental and control strategies and provide, using the log-rank test, assuming an exponential failure rate, 90% power at a 2-sided 5% significance level. The calculation also assumes 17 months of recruitment, a minimum of 33 months of follow-up and a 30% follow-up attrition at the end of year three. Recruitment is assumed to be staggered and builds in seasonal variation. We used the Stata package ARTSURV for calculations [35].

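### The Fig. 1 caption claims power for 25% of all participants crossing over, but the 83% v 92% target covers 25% of the CCR arm only, which is 12.5% of participants in total

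*Protocol article*

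**What the plan says.** The note under Fig. 1 reads: "The study is statistically powered so that up to 25% of participants in total could receive the non-allocated procedure". It adds that processes are in place to keep this from happening.

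The Sample size calculation section starts from three-year vitality of 80% under CCR and 92% under SCR. It defines the problem as "contamination (participants receive the intervention that they were not randomly allocated to"), with no restriction to one arm. It then says: "The team conservatively have allowed for up to 25% contamination". On that basis the trial "aims to detect an absolute improvement of 9%; from 83 to 92% at three years". It continues: "Recruitment of 623 participants (71 events) will detect a hazard ratio of 0.42 between experimental and control strategies", with 90% power by the log-rank test at a two-sided 5% level and exponential failure. The other inputs are 17 months of recruitment, at least 33 months of follow-up and 30% attrition by the end of year three. Allocation is 1:1 (Identifying and recruiting participants).

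**The concern.** The two statements describe different amounts of crossover. The caption counts participants across both arms. The calculation dilutes one arm only, by a quarter of that arm, and leaves the other untouched.

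Crossover is the main threat to the comparison that the protocol names. The Background reports that the two techniques merged in a similar ongoing trial, and a whole section on monitoring fidelity is set against it. A reader who takes the caption at face value would believe that about 156 of 623 participants (25%) could receive the other procedure with 90% power intact. If power is in fact far lower at that level, the stated robustness of the intention-to-treat comparison is one that the design does not have.

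**Working it through.** **Inputs.** All are from the Sample size calculation section except the allocation ratio: 80% v 92% before dilution, 83% v 92% after; N = 623; 71 events; two-sided 5%; exponential failure; 17 months' recruitment; minimum follow-up 33 months; 30% attrition at three years; 1:1 allocation. Two assumptions are mine: accrual is uniform (the protocol says staggered and seasonal) and losses are exponential.

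**Step 1: reproduce the planned figure.** Under exponential survival, HR = ln(0.92)/ln(0.83) = 0.0834/0.1863 = 0.447. For 90% power, Freedman's formula needs 73 events and Schoenfeld's 66. At 71 events power is 89.5% (Freedman) and 92.3% (Schoenfeld). With follow-up running from 33 to 50 months, 623 participants yield about 73 events. So 71 events, 623 participants and 90% power are reproduced for 83% v 92%. The printed hazard ratio of 0.42 differs from 0.447, but that is a separate matter and does not affect this point.

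**Step 2: what crossover does 83% v 92% represent?** 0.75 x 80% + 0.25 x 92% = 83%. The SCR arm stays at 92%. So 25% of the CCR arm crosses over and 0% of the SCR arm does. As a share of all participants this is (25% + 0%)/2 = 12.5%.

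**Step 3: the general relation.** Let c1 be the share of the CCR arm receiving SCR, and c2 the share of the SCR arm receiving CCR.
- Diluted difference = 12 x (1 - c1 - c2) points.
- Share of all participants crossing over = (c1 + c2)/2.

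A 9-point difference requires c1 + c2 = 25%, which is 12.5% of participants for every split. A total of 25% requires c1 + c2 = 50%, which leaves 12 x 0.5 = 6 points for every split.

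**Step 4: power with 623 participants.** Expected events come from the inputs above. Each power range runs from Freedman to Schoenfeld.

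| Crossover | CCR v SCR | HR | Events, follow-up 33-50 months | Power | Power, follow-up capped at 36 months |
|---|---|---|---|---|---|
| 12.5% in total, all in CCR (as planned) | 83% v 92% | 0.447 | 73 | 90-93% | 87-90% |
| 12.5% in total, equal split | 81.5% v 90.5% | 0.488 | 82 | 88-90% | 84-87% |
| 12.5% in total, all in SCR | 80% v 89% | 0.522 | 90 | 85-87% | 81-83% |
| 25% in total, all in CCR | 86% v 92% | 0.553 | 64 | 64-66% | 59-61% |
| 25% in total, equal split | 83% v 89% | 0.625 | 82 | 55-56% | 51-52% |
| 25% in total, all in SCR | 80% v 86% | 0.676 | 99 | 49-50% | 45-46% |

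Holding events at 71 instead gives 37-70% across the three 25% rows. With 25% crossover in each arm, 90% power would need about 191-198 events.

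**The case against.** The caption belongs to a figure that is not shown, and the phrase 'in total' might have been meant as the sum of the two arms' percentages (for example 12.5% + 12.5%). That would match the 9-point target. It is a plausible account of how the wording arose, but a percentage of participants in total does not say that, and the sentence as printed is wrong.

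Several stronger conclusions are tempting and are not supported.

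- A reader might infer that the sample size section is also false. It names no arm and makes no claim about participants overall. A 25% dilution of 12 points is 9 points, and its events and power reproduce. It is unclear, not wrong.
- A reader might infer that the trial's committees would tolerate crossover up to 25%. No section sets a tolerance or an alert level. The fidelity section describes repeated checks on sample teeth, real-time review of case report forms and masked review of radiographs.
- A reader might infer that a null result would be misread. The Proposed analyses section plans causal methods for the primary outcome to estimate efficacy in the presence of crossover. That partly answers the worry, though it does not restore the power of the intention-to-treat comparison.
- A reader might infer from "both treatments are utilised in NHS practice albeit that SCR is relatively under-employed" that reversion to CCR in the SCR arm is the likelier direction. The protocol does not say so. Its account of the similar trial ties merger to each dentist's initial skills and preferences, without a direction.

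The exact power is also less firm than any single number suggests, because it moves with the split, the accrual pattern and the length of follow-up.

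**Conclusion.** The caption states a power property that the design does not have. The 12.5% and 6-point results are algebra from the protocol's own figures and hold for every split under 1:1 allocation. The size of the power loss is approximate: roughly 45-66% at 25% in total, under uniform accrual, exponential events and losses, and follow-up either capped at 36 months or running to 50. No scenario computed, including those with events fixed at 71, exceeds about 70%, so the conclusion that 90% is not protected does not depend on these assumptions. The sample size, the estimand and the analysis are unaffected. What needs correcting is the caption, together with the unstated one-arm assumption in the sample size section.

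**What to change.** Reword the Fig. 1 caption to say: powered at 90% for 25% of the CCR arm (12.5% of participants in total) receiving the non-allocated procedure, with no crossover in the SCR arm. State the same assumption in the Sample size calculation section, where the contamination allowance is introduced.

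Add there that, without a 36-month cap on follow-up, power is about 88-90% if the 12.5% is split equally between arms and about 85-87% if it all falls in the SCR arm. Add also that it is roughly 45-66% at 25% in total, and name the accrual, loss and follow-up assumptions behind these values. The replacement should not describe 12.5% in total as equivalent to 25% of either arm, since 25% of the SCR arm gives less than 90%.

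The cost is wording only. The sample size stays as it is and no new monitoring alert level is needed. The stated robustness to crossover becomes less favourable.

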### Objectives

#### Primary objective

To compare clinical effectiveness and cost-benefit (modelled over a lifetime horizon) of selective caries removal (SCR) with complete caries removal (CCR) in permanent teeth in NHS dental attenders aged 12 years and over who have deep caries in an adult pre-molar or molar tooth.

#### Secondary objectives

To evaluate pulp exposure during caries removal, progression of caries, dental pain and need for dental pain relief, restoration failure and patient oral health-related quality of life.To determine general population preferences for the type of treatment provided and outcomes of care and predict general population barriers to its uptake. To estimate NHS and patient perspective costs, incremental net benefit (willingness to pay minus costs) over three year follow up and incremental cost per Quality Adjusted Life Year (QALY) gained over the three year follow-up and a modelled lifetime horizon.To explore the implementation of technologies and the mechanisms of impact including acceptability

